**Figure 4 figure4:**
[figure not shown]
BPTrack Pharm individual screen.

After baseline data collection is complete, study staff help patient participants download the intervention app onto their smartphone, and train them on how to use the app. Participants are also given a Bluetooth-enabled BP monitor to take home, and are instructed on how to use it, as well as how to sync it to BPTrack. All BP monitors are checked before the patient participant leaves the baseline data collection visit, and are tested against a manual BP reading taken by a trained study staff member. Although we are not calibrating the home BP monitors, we do look to see how well their readings compare with the manual BP readings. Once enrolled in the study, the clinical pharmacist sees patient participants as needed for ongoing HTN management.

Patient participants are also instructed on the BP monitoring protocol that we will adhere to in this study, and are instructed to take three consecutive BP readings twice daily, at varying times across days. Prior to BP monitoring, patient participants are instructed to: go to the bathroom before taking their BP, if needed; keep their arm at heart level by resting it on a table during monitoring; sit in a chair with a back, with feet flat on the floor for at least five minutes prior to monitoring; avoid tobacco, caffeine, or alcohol for 30 minutes prior to BP monitoring; avoid taking their BP immediately after exercise, when emotionally upset, or in pain; and to avoid talking while taking their BP.

In the event that a patient participant has an SBP >160 mmHg, SBP <100 mmHg, DBP >100 mmHg, or DBP <60 mmHg, they are instructed to wait five minutes and then recheck their BP using the previously described protocol. Patient participants are also instructed that if BP readings exceed these critical thresholds for three days in a row, they should contact the clinic. Finally, patient participants are instructed to call the clinic immediately if they are experiencing symptoms of dizziness, chest pain, severe headache, or visual changes.

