Patient participants are instructed to follow the home BP monitoring protocol for 12 weeks, to ensure that the BP readings sync with the BPTrack app, and to self-monitor BP medication adherence. During this 12-week intervention period, the project’s clinical pharmacist monitors home BP and medication adherence readings through the BPTrack Pharm clinician app, and manages patient participant HTN in concordance with their normal clinical practice. In the event that a patient participant exhibits continued elevated BP readings, the clinical pharmacist contacts them to determine whether the patient needs to come in to the clinic for follow-up, or whether to continue to monitor through the app. The clinical pharmacist is exercising their best clinical judgment in managing the research participants’ BP.

At the conclusion of the 12-week intervention period, patient participants meet with study staff for their 12-week follow-up data collection visit, which takes approximately 60 minutes to complete. At this visit, the patient participants complete the Adherence to Refills and Medications Scale (ARMS) [19], they are asked to bring in all antihypertensive medications for a pill count, and interviews are audio recorded.

To compensate patient participants for their participation in the study and to reduce attrition, individuals receive US $25 upon completion of their 12-week follow-up data collection visit. Patient participants are also allowed to keep the BP monitor used in the study (valued at approximately US $100/monitor). In addition to incentives offered for participation, additional retention strategies implemented in past and current projects are being used, such as routinely obtaining contact information for the participant and up to three friends/relatives who can help locate them, as well as baseline and follow-up appointment reminders via phone and/or email. Individuals who leave the study early are compensated on a pro-rated basis, and are required to return the BP monitor.

After the study has finished, we will conduct interviews with the study’s clinical pharmacist and other key stakeholders at the recruiting clinical site. Key stakeholders will be recruited through direct solicitation via email and phone calls; these stakeholders are expected to include clinic medical directors, primary care physicians, health systems administrators, and information technology personnel. These interviews will be audio recorded and transcribed for further analysis.

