### Statistical Analysis Plan

Descriptive statistics will be used to describe patient participant characteristics and perceptions, mHealth utilization, and clinical pharmacist utilization and perceptions. Categorical data will be displayed as frequencies and percentages, and Chi-square tests will be used for comparisons. SBP and DBP will be expressed as mean (standard deviation) and pre/postintervention BP means will be compared using 2-tailed paired samples t-tests.

The effect of clinical pharmacist contact with patient participants will be evaluated through changes in utilization of the mHealth app and changes in BP levels surrounding the time of contact. Models will be used to separately evaluate SBP and DBP levels over time, including pharmacist contact as a time-varying covariate using a mixed-effects regression approach. The mixed-model analysis accounts for the correlation of BP measures on the same individual across time. Similar analyses will be carried out on daily utilization of the mHealth app. Daily usage will be coded as a binary response and modeled using generalized estimating equations, including pharmacist contact with patient participants as a covariate to identify the odds of app usage before and after contact.

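### Pharmacist contact is prompted by high BP, so an effect of contact read from BP around the contact, or from an ordinary time-varying covariate, can be spurious unless contact is lagged and prior BP is conditioned on

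*Protocol article*

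**What the plan says.** The Statistical Analysis Plan section states the target in causal terms: "The effect of clinical pharmacist contact with patient participants will be evaluated through changes in utilization of the mHealth app and changes in BP levels". The window is "changes in BP levels surrounding the time of contact". The method is separate models for SBP and DBP, "including pharmacist contact as a time-varying covariate using a mixed-effects regression approach". The one property claimed for the model is this: "The mixed-model analysis accounts for the correlation of BP measures on the same individual across time".

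The Procedures section describes how contact comes about. During the 12 weeks the "clinical pharmacist monitors home BP and medication adherence readings through the BPTrack Pharm clinician app". Then: "In the event that a patient participant exhibits continued elevated BP readings, the clinical pharmacist contacts them", to decide between a clinic visit and further monitoring. Timing is discretionary: "The clinical pharmacist is exercising their best clinical judgment in managing the research participants’ BP". Patients are also told that "if BP readings exceed these critical thresholds for three days in a row, they should contact the clinic"; those limits include low as well as high values. Visits to the pharmacist take place as needed.

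The article mentions no adjustment for the BP history behind a contact and does not describe this analysis as descriptive. The Limitations section concedes the small sample and the lack of a control group, but not this point.

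**The concern.** Contact depends on earlier values of the outcome it is meant to explain. Two distortions follow, with opposite signs.

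- **Regression to the mean.** Contact is made when BP is at a temporary high, so later readings tend to be lower than the triggering ones even if contact does nothing. A before/after reading makes contact look helpful.
- **Confounding by indication.** BP is autocorrelated, so in the days after a high run it is still above the patient's usual level. A model that compares those days with the patient's other days makes contact look harmful.

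A random intercept removes stable differences between patients. It does not remove the dependence of contact on recent BP within a patient.

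This is the article's only planned quantitative analysis of how BP responds to pharmacist action, and the pilot is meant to inform later work. A coefficient whose sign reflects coding rather than care would be a poor basis for that.

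**Working it through.** **Is there a figure to reproduce?** No. The article gives no SD, effect size, alpha or power for this analysis. The check is therefore structural, followed by simulation with a true contact effect of zero.

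**Inputs from the article.** Up to 25 patients; 12 weeks, or 12 × 7 = 84 days; contact follows persistently high readings.

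**Assumptions, not in the article.** Mean SBP 142 mmHg; between-patient SD 10; within-patient deviations AR(1) with SD 6 or 10 and daily correlation ρ of 0.3 to 0.9; extra measurement SD 5; contact on the day after three consecutive daily values above 140, at most once per 14 days.

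**Why both signs arise.** Under AR(1), a true deviation d on the last triggering day has expected size ρ^k·d after k days. Its mean over the next 7 days is d × ρ(1 − ρ^7)/[7(1 − ρ)].

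- ρ = 0.3: 0.3 × 0.9998/(7 × 0.7) = 0.06 d
- ρ = 0.6: 0.6 × 0.9720/(7 × 0.4) = 0.21 d
- ρ = 0.9: 0.9 × 0.5217/(7 × 0.1) = 0.67 d

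The following week is thus above the patient's own level by 0.06 to 0.67 d and below the triggering day by 0.94 to 0.33 d. As ρ rises, the spurious regression coefficient should grow and the spurious fall should shrink.

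**Simulation of the random-intercept model.** Fitted model: SBP = patient intercept + day + contact. Each row is 40 simulated trials. Coefficients are in mmHg, with rejection at 0.05 in brackets.

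| Scenario | Contact = 7 days from contact | Contact = ever contacted | 7 days after minus 3 triggering days | 7 days after minus 7 days before |
|---|---|---|---|---|
| ρ 0.3, SD 6 | +0.34 (15%) | −0.06 (5%) | −3.20 | −0.43 |
| ρ 0.3, SD 10 | +0.55 (20%) | +0.34 (15%) | −5.87 | −0.86 |
| ρ 0.6, SD 6 | +0.87 (55%) | +0.45 (25%) | −2.92 | −0.20 |
| ρ 0.6, SD 10 | +2.08 (82%) | +0.90 (20%) | −4.80 | +0.11 |
| ρ 0.9, SD 6 | +1.95 (98%) | +2.08 (75%) | −1.79 | +0.04 |
| ρ 0.9, SD 10 | +4.44 (100%) | +4.84 (88%) | −2.21 | +0.63 |
| ρ 0.6, SD 10, trigger 150 | +2.37 (90%) | +0.83 (22%) | −8.08 | −1.36 |
| ρ 0.6, SD 10, contact unrelated to BP | −0.12 (15%) | +0.16 (22%) | −0.32 | −0.31 |

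Three points on reading the table:

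- When contact is unrelated to BP, the coefficients are near zero, so the trigger is the cause of the bias.
- In that same row the test still rejects in 15% and 22% of trials, because a random intercept alone ignores serial correlation. The rejection rates therefore mix two faults, and the coefficients are the cleaner evidence. With 40 trials, a rate of 15% has a standard error of √(0.15 × 0.85/40) = 5.6 points.
- The before/after fall depends on the window. It is large against the triggering days and small against a full prior week.

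**Simulation with serial correlation modelled.** Assumptions: mean 145; between-patient SD 10; contact when the 3-day mean exceeds 155; a 7-day indicator starting the day after the trigger; 40 trials per row.

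| Scenario | Random intercept only | Plus AR(1) residual and measurement noise |
|---|---|---|
| ρ 0.5 | +1.6 (72%) | +0.03 (5%) |
| ρ 0.8 | +4.9 (100%) | +0.16 (12%) |
| ρ 0.9 | +6.5 (100%) | +0.27 (5%) |
| 30% of triggers acted on | +3.3 (100%) | +0.11 (12%) |

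If the indicator included the trigger day, the bias stayed at +4.0 mmHg (100%). A further set of runs agreed. Random intercept only gave +1.1 to +4.8 mmHg (40–100%). Lagged contact with serial correlation gave −0.2 to 0.0 mmHg (4–8%). Including the trigger day gave +2.4 mmHg (96%).

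So both conditions are needed. In the first table contact already starts after the triggering readings, yet the random-intercept model is biased. In these last runs serial correlation is modelled, yet including the trigger day brings the bias back.

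**Landmark comparison.** Mean BP over the next 7 days was regressed on contact, trailing 3-day and 7-day mean BP, study day and patient. In two sets of zero-effect runs the bias was at most about 0.16 mmHg, with rejection of 3–9% and 5–12%.

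**The case against.** The strongest reply is that the article does not commit to a random intercept. It says mixed-effects regression that accounts for within-person correlation, which can include a serial residual structure. If contact depends only on recorded past BP, a correctly specified likelihood conditions on that past, and the simulations bear this out. A reader might infer that any mixed model with contact as a time-varying covariate must fail, or that this one is certain to report a false effect. The documents do not support that: the bias is a strong risk under some readings of the text and nearly absent under another.

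It is also fair that covariance structure, lag and coding are details an article may leave to a fuller plan. Their absence is not the finding. The finding is what the article does state: a causal target, a window surrounding the contact, and contact driven by the outcome.

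Other inferences to resist:

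- **That a raw before/after contrast is definitely planned.** The phrase about BP around the contact may only describe the aim that the mixed models carry out.
- **That every contact follows high BP.** Visits are as needed, judgment enters, and low readings or symptoms can prompt calls to the clinic. This dilutes the bias; acting on only 30% of triggers still left +3.3 mmHg in the random-intercept model.
- **That the app-use analysis shares the fault.** It could if missing readings prompted contact, but the article states no such trigger.
- **That the pilot's conclusions are at risk.** Its objectives are feasibility and acceptability, and it admits it may lack power to detect effects.

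**Conclusion.** The point holds as a risk in a secondary analysis that should be corrected. With no true effect, comparing the week after contact with the triggering days shows a spurious fall of about 2 to 6 mmHg in most scenarios. A random-intercept model, or a coding that includes the trigger day, shows a spurious rise of about 0.3 to 6 mmHg, often significant. The exception in the table is the ever-contacted coding at the weakest autocorrelation and smaller SD, where the coefficient was about zero. All sizes rest on assumed SDs, autocorrelation and trigger levels, with few replicates per scenario. The direction and mechanism follow from the contact rule in the Procedures section together with autocorrelated BP. Lagging contact and modelling serial correlation together largely remove the bias, provided the correlation form is adequate and contact depends only on recorded BP.

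**What to change.** In the Statistical Analysis Plan section, start the contact indicator after the readings that prompted contact, and condition on that BP history in one of two ways:

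1. **Landmark comparison.** For each patient-day, model mean BP over the next 7 days on contact that day, adjusting for trailing 3-day and 7-day mean BP, study day and patient, with standard errors clustered by patient. This sets contacted days against equally elevated days without contact.
2. **Mixed model.** Keep it, with a lagged contact term and a serial residual structure, for example AR(1) plus measurement error.

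State that an unadjusted before/after change will not be interpreted as an effect, and report the result as an association. The pharmacist also sees adherence data and uses judgment, so prompts other than BP may remain.

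The data are already to be collected: home readings from the cloud server and contacts from the chart review. The cost is a few lag variables and some precision. In the landmark version the first 7 days serve only as history, and requiring a full 7-day outcome leaves at most 84 − 7 − 7 = 70 usable days per patient.

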## Results

Patient participant recruitment for the pilot study began in November 2016, and data collection is expected to conclude in late-2017.

## Discussion

### Principal Results

At the conclusion of this study, we expect to be able to demonstrate the feasibility and acceptability of using an mHealth approach for supporting clinical pharmacist-led HTN management in a primary care clinic. By placing clinically relevant home BP and medication adherence data from patients directly into the hands of a medical professional who has the potential to act upon it in a clinically relevant and timely manner, we may be better able to improve patient care for individuals who struggle to manage HTN. Moreover, by incorporating mobile devices that are already used by the target population, we are taking an inherently patient-centered approach to HTN management. This “bring-your-own-device” approach ensures that we are asking people to utilize technologies already incorporated into daily life, which is necessary for adequate translation from bench to bedside. We anticipate that through this pilot study, we may be able to document efficiencies that this type of program may create, and learn from our stakeholders how to overcome barriers to implementation and adoption, in advance of a larger scale roll-out.

### Limitations

Perhaps the largest limitation of this pilot study is our limited sample size, which was chosen due to the pragmatics of recruitment and budgetary constraints. As highlighted by Leon et al, “the primary role of a pilot study is to example the feasibility of a research endeavor” [21]. Our intended sample size is large enough to satisfy the rule of thumb of 12 participants per group (set forth by Julious et al [22]) as appropriate for guiding sample size selection for pilot studies. Although we may not have adequate power to detect effects, this is a true feasibility trial in which we will be able to obtain preliminary data to support and plan for future implementations. Feasibility will be assessed on many different levels, including the feasibility of using BPTrack amongst our target population, within the primary care setting, and within the health system. In addition, the lack of a control or other comparison group is a limitation of our study design; however, given that this is a pilot study to preliminarily investigate the use of this approach in a clinical setting, our single group design is warranted. Future work should seek to incorporate a more robust research design.

### Comparison to Prior Work

This type of clinical pharmacist-led mHealth approach to improving HTN management has been demonstrated to be effective within research settings. Although it was undertaken in a different population, a recent study by Margolis et al found that 57.2% of participants randomized to receive an intervention that involved pharmacist case management for HTN, plus home BP telemonitoring, were able to bring their BP down to controlled levels at 6 and 12 months, versus 30.0% of those receiving usual care [13]. Moreover, at 6-months postintervention, 71.8% of intervention participants had controlled BPs versus 57.1% in usual care [13]. These findings provide strong evidence in support of this approach, yet their study was limited to a research setting, and was not integrated into routine clinical practice. Our pilot study seeks to lay the foundation for translating the Margolis et al findings into practice [13].

### Conclusion

This pilot study was designed to document the feasibility and acceptability of a clinical pharmacist-led mHealth approach to managing HTN within a primary care setting. In our 12-week pilot study, we expect to lend support for this approach and lay the foundation for translating this approach into wider-scale implementation, in order to leverage the multidisciplinary care team already in place within primary care, and to improve health outcomes for patients with uncontrolled HTN.

## Appendix

Multimedia Appendix 1 MICR peer review report 1.

Multimedia Appendix 2 MICR peer review report 2.

## Abbreviations

ARMS: Adherence to Refills and Medications Scale
BP: blood pressure
DBP: diastolic blood pressure
HTN: hypertension
mHealth: mobile health
SBP: systolic blood pressure
